# Intravenous ferric carboxymaltose versus oral ferrous sulphate for the treatment of moderate to severe postpartum anaemia in Nigerian women (IVON-PP): protocol for an open-label randomised controlled type 1 hybrid effectiveness-implementation trial

**DOI:** 10.1136/bmjopen-2024-086553

**Published:** 2024-08-14

**Keywords:** quality of life, depression & mood disorders, postpartum women, anaemia

## Abstract

**Introduction:**

Postpartum anaemia is often caused by iron deficiency with onset during the antepartum period and can be exacerbated by excessive blood loss at birth. Its prevalence is estimated as 50–80% in low-income and middle-income countries. It poses adverse consequences on the mother and negatively impacts her ability to care for her newborn. Prompt treatment of postpartum anaemia is thus important. Adherence to oral iron is reportedly low in Nigeria due to its side effects and forgetfulness by the mothers. Intravenous iron such as ferric carboxymaltose, given as a single dose, might help overcome adherence issues, but investigation in a high-quality randomised control trial in Nigeria is first required while evaluation of challenges around its implementation is also warranted.

**Objective:**

To determine the clinical effectiveness, tolerability and safety, of using intravenous ferric carboxymaltose (intervention) vs oral ferrous sulphate (control) for treating moderate to severe iron deficiency anaemia in postpartum women and to evaluate implementation of ferric carboxymaltose in treating postpartum anaemia in Nigeria.

**Methods and analysis:**

This study is an open-label randomised controlled trial with a concurrent implementation study. It is a hybrid type 1 effectiveness-implementation design conducted in four states across Northern and Southern Nigeria. A total of 1400 eligible and consenting women with postpartum moderate to severe anaemia (haemoglobin concentration <100 g/L) will be randomised to intravenous ferric carboxymaltose; a single dose at 20 mg/kg to a maximum of 1000 mg infusion administered at enrolment (intervention) or oral ferrous sulphate; 200 mg (65 mg elemental iron) two times per day from enrolment until 6 weeks postpartum (control). The primary outcome, proportion of participants who are anaemic (Hb <110 g/L) at 6 weeks postpartum will be analysed by intention-to-treat. Haemoglobin concentration, full blood count, serum iron, serum ferritin, transferrin saturation and total iron binding capacity will be measured at specific intervals. Implementation outcomes such as acceptability and feasibility of using ferric carboxymaltose for postpartum anaemia treatment in Nigeria will be assessed.

**Ethics and dissemination:**

This study is approved by the ethics committee of the teaching hospitals, Ministry of Health of the four states as required, National Health Research Ethics Committee and the drug regulatory agency, National Agency for Food and Drug Administration and Control (NAFDAC). Findings of this research will be presented at conferences and will be published in international peer-reviewed journals and shared with stakeholders within and outside Nigeria.

**Trial registration number:**

International standard randomised controlled trial number: ISRCTN51426226.

STRENGTHS AND LIMITATIONS OF THIS STUDYMulticentre randomised controlled trial conducted across diverse regions of Nigeria.Hybrid design evaluating effectiveness as well as implementation contexts and outcomes.Open-label design.Self-reported measures of adherence and some secondary outcomes.Generalisability is limited to similar populations and health systems.

## Introduction

### Background and rationale

 Maternal anaemia is a major public health burden with a high incidence in low-income and middle-income countries (LMICs).^1 2^ Iron deficiency causes more than half of all cases.^1^ Postnatal anaemia may result from untreated antenatal anaemia or blood loss around the time of birth.^3^ Its prevalence in LMICs has been estimated to range from 50% to 80%.^4^ A study in Eastern Nigeria found anaemia at 48 hours and 6 weeks postpartum to be 73% and 48%, respectively, in a cohort of 202 women followed from late pregnancy to 6 weeks postpartum.^5^ The consequences of postnatal anaemia are substantial. Postnatal anaemia increases the risk of infection and poor wound healing, and may cause fatigue and/or depression in the mother.^6^ It also adversely affects breastfeeding due to insufficient milk production and can reduce bonding between women and their newborn because of weakness and fatigue.^3 4 7^

Oral iron is used routinely for the treatment of mild to moderate anaemia soon after birth and up to 42 days, while blood transfusion is offered for severe anaemia or symptomatic women with moderate anaemia.^3^ Oral iron, though inexpensive, causes significant gastrointestinal adverse effects such as vomiting, constipation, diarrhoea and abdominal pain.^8^ This limits adherence to iron supplementation and poses a challenge to achieving optimal and timely correction of anaemia, as has been shown among pregnant women.^9 10^ In a large population-based study in 22 Sub-Saharan African countries, only 22.9% of Nigerian women had greater than 90 days of iron supplementation during pregnancy with their most recent birth.^11^

Whether intravenous iron can be a suitable alternative to oral iron for the treatment of postnatal anaemia is unclear. Intravenous iron can be given as a single dose and is suitable for patients who respond poorly to oral iron and are unable to tolerate the side effects, and moderately anaemic women that require more rapid iron replacement.^3^ Intravenous iron corrects anaemia faster and in fewer doses than oral iron and requires fewer patient-provider interactions.^1^ Intravenous iron is therefore optimal for LMICs where women do not routinely attend postnatal follow-up visits.^1^ Previous randomised trials of intravenous iron for postpartum anaemia have reported faster and more effective correction of anaemia compared with oral iron.^12^ These studies have been small, and none were conducted in an African setting.^12 13^ These studies also considered different formulations for intravenous iron including ferric carboxymaltose (FCM), iron sucrose and ferrous sulphate. ^13^FCM is convenient to administer as it can be administered in a single dose and is also associated with low amounts of potentially harmful non-transferrin bound iron.^13^ Thus, the safety and efficacy profile of FCM makes it an ideal formulation for this purpose.

This study aims to determine the effectiveness, tolerability and safety of intravenous FCM (intervention) vs oral ferrous sulphate (control) for treating moderate to severe iron deficiency anaemia in postpartum women (population). We also aim to evaluate implementation of FCM in treating postpartum anaemia in Nigeria. Our objectives are:

To determine the effectiveness of FCM vs oral ferrous sulphate in postpartum women with moderate to severe iron deficiency anaemia by conducting a randomised trial.To determine the incidence of adverse drug events including the incidence of hypophosphataemia in the postpartum women and adherence to oral ferrous sulphate for treatment of postpartum anaemia.To evaluate the acceptability and feasibility of using intravenous FCM in treating postpartum anaemia in Nigeria by conducting a concurrent implementation study.

## Methods and analysis

### Study design

The IVON-PP trial uses a hybrid effectiveness-implementation design to assess intervention effectiveness and collect contextual information for implementation.^14^ A multicentre, parallel, open-label, superiority randomised controlled trial aimed to compare the effectiveness and safety of FCM (intervention) and ferrous sulphate (standard care) in treating iron deficiency anaemia among postpartum Nigerian women is being conducted. As the effectiveness of FCM is being assessed through various outcome measures, an implementation study will be conducted simultaneously to explore its acceptability and feasibility (implementation outcomes) (figure 1).

**Figure 1 F1:**
[figure not shown]
Flow chart of IVON-PP implementation-effectiveness hybrid type 1 trial design.

### Study sites

The study is being conducted in 20 recruiting sites in four states in Nigeria: Kano and Kwara states in the North, and Lagos and Rivers states in the South (figure 2). In each state, one tertiary, three secondary and one primary healthcare facilities are participating. The list of study sites can be obtained from the trial registry (ISRCTN51426226).

**Figure 2 F2:**
[figure not shown]
Map of Nigeria indicating the four selected study states with key population and service indices.

### Eligibility criteria

Inclusion criteria:

Women aged between 15 and 49 years and between 6 and 48 hours after birth.Moderate or severe anaemia (haemoglobin <100 g/L), confirmed by Hemocue haemoglobinometer.Able and willing to give written informed consent.

Exclusion criteria:

Blood transfusion, for any indication, within the last 3 months.Symptomatic anaemia and a need for urgent correction.Known haemoglobinopathy such as sickle cell disease, haemoglobin C disease.Clinically confirmed malabsorption syndrome.Known hypersensitivity or contraindication to any form of iron treatment, study drug or any of its excipients.Self-reported pre-existing maternal depression or other psychiatric illness as evidenced by a YES response to any history of psychiatry ward hospitalisation, psychiatry medications, behavioural changes or past consultation with psychiatric services.Severe allergic conditions such as severe asthma, eczema, or other atopic conditionKnown autoimmune conditions for example, systemic lupus erythematosus, rheumatoid arthritis or known severe drug allergies.Planning to move or reside outside the research area within the study period.

### Interventions

The intervention, FCM is given as a single dose of 20 mg/kg up to a maximum of 1000 mg diluted in 200 mL normal saline and infused over a minimum of 15–20 min. Eligible women randomised to the intervention arm (FCM) are administered the intravenous iron within 6–48 hours after delivery at the dedicated ward or daycare room, where she is also observed post infusion. The control drug, oral ferrous sulphate is given as one 200 mg tablet, which contains 65 mg of elemental iron, two times daily to be taken 1 hour before meals or 2 hours after meals with a full glass of water until 6 weeks postpartum. Women in both groups will have folic acid (5 mg daily) and vitamin C (200 mg two times per day). If a woman suffers severe adverse drug event up to grade 3, the study drug may be discontinued.

### Adherence

Women randomised to the control group are sent automated daily text messages as reminders to take their medication. They are asked to bring their pill sachets to each clinic or home visit for pill counting to calculate adherence. The empty pill packs are collected and labelled with the participant’s ID and archived at the trial site.

### Adverse drug event monitoring

Adverse drug events are closely monitored and recorded. At each clinic or home visit, women are asked of any symptom that has occurred and asked to report symptoms between study visits. Adverse drug events are documented according to the severity, duration, grade, relationship to trial drugs, interventions given and the outcome. The costs of treating all adverse drug events related to trial drugs are borne by the trial.

### Clinical outcomes

The primary outcome is the proportion of participants who are anaemic (haemoglobin < 110 g/L) at 6 weeks postpartum.

Secondary outcomes:

Change in mean serum ferritin, serum transferrin, serum iron and % transferrin saturation at 2 weeks and 6 weeks postpartum.Proportion of women with postpartum depression, measured using the Edinburgh Postnatal Depression Scale (EPDS)^15^ at 6 weeks and 6 months postpartum.Change in mean postpartum haemoglobin levels at 2 weeks and 6 weeks postpartum.Achievement of a non-anaemic state (Hb ≥110 g/L) at 6 months postpartum.Prevalence of moderate/severe anaemia at 6 weeks and 6 months postpartum. Moderate anaemia is defined as haemoglobin level 70–<100 g/L and severe anaemia as haemoglobin level <70 g/L.Need for blood transfusion after iron treatment during the first 6 weeks postpartum.Prevalence of fatigue at 6 weeks and 6 months postpartum, measured using the Fatigue Severity Scale (revised FSS-5R version).^16^Proportion of women with secondary postpartum haemorrhage after treatment. This will be defined as excessive bleeding requiring surgical intervention or blood transfusion from 24 hours after delivery until 12 weeks postpartum.Proportion of infants being breastfed (exclusive and any) at 6 weeks and 6 months postpartum.Prevalence of impaired maternal-infant bonding at 6 weeks and 6 months postpartum measured using the Mother-to-Infant Bonding Scale.^17^Incidence of confirmed or suspected maternal infection within 6 weeks of birth, as defined by a new prescription of antibiotics for presumed perineal wound-related infection, endometritis or uterine infection, urinary tract infection or other systemic infection (clinical sepsis).Incidence of hypophosphataemia at 2 weeks and 6 weeks postpartum. We will measure vitamin D, alkaline phosphatase, procollagen type I N-terminal propeptide (P1NP), fibroblast growth factor 23 (FGF23), calcium, phosphate, all of which are biomarkers of phosphorus homeostasis and bone turnover. Hypophosphataemia is defined as serum phosphate level <2.5 mg/dL (0.81 mmol/L). Mild hypophosphataemia as 2–2.5 mg/dL (0.65–0.81 mmol/L), moderate as 1–2 mg/dL (0.32–0.65 mmol/L) and severe as <1 mg/dL (0.32 mmol/L).Incidence of early neonatal death, defined as death of newborn from enrolment of the mother to before seven completed days.Incidence of late neonatal death, defined as death of the newborn after seven completed days of birth to before 28 completed days.Incidence of infant death, defined as death from enrolment before the age of 6 months.Incidence of postnatal maternal death from enrolment up to 6 weeks and at 6 months postpartum.Incidence of adverse drug events.Quality of life measured using the WHO Quality of Life BREF^18^ at 6 weeks and 6 months postpartum.

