### Sample size

We used data from a recent meta-analysis,^19^ which reported that 39% of women were anaemic at 6 weeks postpartum, as the control event rate. A sample size of 697 participants per group would provide 90% power to detect a relative reduction of 20% for intravenous iron to reduce the event rate of anaemia at 6 weeks postpartum to 30%, after accounting for 10% loss to follow-up. Power calculations assume a 1:1 randomisation ratio to each of the two treatment arms. 1400 women will be enrolled into the trial.

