### Statistical methods and analysis

Primary analyses will be conducted with the intention to treat principle. Categorical variables will be expressed as frequencies and percentages. Continuous variables will be presented as means (SD) or medians (interquartile ranges) depending on whether they are normally distributed or not. The effect of intravenous iron (vs oral iron) on the primary endpoint will be analysed using log-binomial regression models to obtain relative risks, 95% CIs and p values. The impact of clustering by site will be evaluated by comparing to logistic generalised linear mixed models using likelihood ratio tests, and the more parsimonious model presented. The extent to which inclusion of baseline covariates modifies the precision of estimates will be explored. Generalised linear mixed models will be used to estimate the effect of the treatment arm on repeated measures of haemoglobin and iron status biomarkers. The proportion of participants who are anaemic or iron deficient, and the proportion of participants who achieve anaemia correction at 6 weeks and 6 months follow-up will be compared. Subgroup analyses will be conducted to compare study findings by region (Lagos, Kwara, Kano and Rivers), mode of birth (caesarean vs vaginal birth) and by the occurrence of primary postpartum haemorrhage. A two-tailed test of hypothesis will be performed based on an alpha level of 0.05. R and RStudio (2020)http://www.rstudio.com/ will be used for statistical analysis.^20^ An interim analysis will be conducted by an independent statistician after achieving 50% of the sample size and data presented to the Data Safety and Monitoring Board (DSMB). Based on O’Brien-Fleming method,^21^ the threshold for significance of the primary endpoint at the interim analysis will be alpha=0.0054. The clinical trial will be terminated if the null hypothesis is rejected. The alpha level for the analysis at the end of the study will be adjusted to 0.0492 based on alpha adjustment based on O’Brien-Fleming method.

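### Depression, fatigue and bonding are defined only as yes/no proportions, which discards at least about a third of the score information and makes a real symptom benefit easier to miss

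*Protocol article*

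**What the plan says.** Under Clinical outcomes in the protocol article, three questionnaires that yield graded scores enter the list of secondary outcomes as proportions:

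- Fatigue: "Prevalence of fatigue at 6 weeks and 6 months postpartum, measured using the Fatigue Severity Scale (revised FSS-5R version".
- Bonding: "Prevalence of impaired maternal-infant bonding at 6 weeks and 6 months postpartum measured using the Mother-to-Infant Bonding Scale".
- Depression: the proportion of women with postpartum depression on the EPDS, also at 6 weeks and 6 months.

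No cut-off, expected prevalence or mean-score outcome is printed for any of the three. The same list treats haemoglobin differently: "Change in mean postpartum haemoglobin levels at 2 weeks and 6 weeks postpartum". Under Statistical methods and analysis, mixed models are planned for repeated haemoglobin and iron markers, and no model is named for scale scores. Data collection methods says that the three scales are captured as electronic forms in the trial database.

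**The concern.** A prevalence needs each woman classed as affected or not. Once that is done, a woman just over the line counts the same as one far beyond it, and an improvement that does not cross the line counts for nothing. The comparison then needs more women to detect the same shift.

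These outcomes carry weight. The Background names fatigue and depression as possible consequences of postnatal anaemia and weakened bonding as another. Patient and public involvement records that the fatigue and bonding scales were added after feedback. The primary endpoint is a laboratory threshold, so these scales are a large part of the evidence on whether women feel better. A non-significant difference in proportions could be read as no felt benefit when the scores would have shown one.

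**Working it through.** **Inputs from the article.** Sample size: "A sample size of 697 participants per group would provide 90% power", with 10% loss to follow-up. Control rate for the primary outcome: the meta-analysis "which reported that 39% of women were anaemic at 6 weeks postpartum, as the control event rate", against 30% with intravenous iron. Test level: "A two-tailed test of hypothesis will be performed based on an alpha level of 0.05". For the final analysis, "The alpha level for the analysis at the end of the study will be adjusted to 0.0492".

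**The plan's own figure.** For 39% against 30%, two-sided 0.05 and 90% power, the plain two-proportion formula gives 585 per arm, and 585/0.9 = 650. With continuity correction and alpha 0.0492 it gives 609, and 609/0.9 = 677, which is 2.9% below 697. So 697 is only roughly reproduced. It concerns the primary outcome and is used here only for the number of evaluable women: 697 × 0.9 = 627 per arm.

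**Assumptions, not in the article.** A roughly normal score; treatment shifts the mean and leaves the spread unchanged; control prevalence p between 10% and 50%; two-sided alpha 0.05 for these secondary outcomes.

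**Step 1: information kept by the split.** For small shifts, the efficiency of the binary form relative to the score is φ(z)² / [p(1 − p)], where z is the cut-off that a proportion p exceeds and φ is the standard normal density. At p = 0.20, z = 0.8416 and φ(z) = 0.2800, so efficiency = 0.0784/0.16 = 0.49.

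**Step 2: a reference shift.** The shift that the score detects with 80% power is d = (1.960 + 0.842) × √(2/627) = 0.158 SD.

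**Step 3: power of the proportions for that same shift.** The treated proportion is p₂ = 1 − Φ(z + 0.158), and power is Φ{[(p − p₂)√n − 1.96√(2p̄(1 − p̄))] / √(p(1 − p) + p₂(1 − p₂))}, where p̄ is the average of p and p₂. At p = 0.20, p₂ = 0.1587; the numerator is 1.035 − 1.063 = −0.028, the denominator is 0.542, and power is Φ(−0.05) = 0.48.

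| Assumed control prevalence | Information kept | Information lost | Proportions compared | Power, binary | Power, score |
|---|---|---|---|---|---|
| 50% | 64% | 36% | 50.0% vs 43.7% | 61% | 80% |
| 40% | 62% | 38% | 40.0% vs 34.0% | 59% | 80% |
| 30% | 58% | 42% | 30.0% vs 24.7% | 55% | 80% |
| 20% | 49% | 51% | 20.0% vs 15.9% | 48% | 80% |
| 10% | 34% | 66% | 10.0% vs 7.5% | 35% | 80% |

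The loss is smallest at 50% prevalence. By the Step 1 formula it reaches half at a prevalence of about 21% (or, by symmetry, 79%).

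**Step 4: a larger shift.** At 0.20 SD with 630 per arm (90% of 700), the score has 94% power. The binary form has 81%, 79%, 75%, 67% and 50% at control prevalences of 50%, 40%, 30%, 20% and 10%. The gap persists, but at the higher prevalences the binary form is then reasonably powered.

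**The case against.** **Proportions are legitimate and easy to interpret.** This is true, and nothing in the list is contradictory. It is a reason to keep the proportions, not to make them the only listed form.

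**Score analyses and cut-offs may be in the SAP.** They may, and the absence of a cut-off is not counted against the article. What is challenged is the outcome form that the article does state. If the SAP already specifies mean-score comparisons, the point is met.

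**The size of the loss is uncertain.** This stands. A reader might infer that half or more is always lost. The documents do not support that: they give no prevalence, and fatigue could be common in women enrolled with haemoglobin below 100 g/L, where the loss would be nearer 36% to 42%. The normal model is also only approximate for bounded, possibly skewed questionnaires.

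**A null result is not shown to be likely.** This also stands. The 35% to 61% range follows from choosing a shift that gives the score exactly 80% power. The article states no expected effect, and Step 4 shows better power at 0.20 SD.

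**Timing.** A reader might go further and say that the scales miss the 2-week visit, where benefit ought to appear. The Background says "Intravenous iron corrects anaemia faster and in fewer doses than oral iron", but that concerns anaemia and does not say when symptoms respond. Poor adherence to oral iron is also part of the rationale, and a difference from that source could show at 6 weeks. The participant flow figure is not shown. Adding a scale at 2 weeks is no longer a realistic remedy either: recruitment was projected to end by June 2024 and the article is dated 14 August 2024.

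**Another patient-reported outcome is listed.** Quality of life (WHOQOL-BREF) is not tied to a threshold, which softens the risk. It does not replace the three specific scales.

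**Conclusion.** The point holds for the outcome form. As worded, the three scales are compared only as proportions. Under a roughly normal score this loses at least about a third of the information, and half or more if prevalence is about 21% or lower. For a shift that the score would detect with 80% power with 627 women per arm, power falls to between 35% and 61% across assumed prevalences of 10% to 50%. No prevalence makes the binary form as efficient as the score under this model, so a real symptom benefit is more likely to be missed. It is not established that it will be missed. The calculation rests on assumed prevalences, an assumed shift and approximate normality. These are secondary outcomes, and the primary conclusion does not depend on them.

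**What to change.** Before unblinding, state in the Clinical outcomes section and in the SAP that EPDS, FSS-5R and the Mother-to-Infant Bonding Scale will each be compared between arms on mean total score at 6 weeks and at 6 months. Report alongside, for each scale, the proportion above a cut-off fixed at the same time. If the scores prove markedly skewed, the SAP should say how the comparison will be adapted.

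The cost is small: the scales are already captured, so only outcome and SAP wording changes. The downsides are a result in scale points, which is less direct than a percentage, and a change to stated secondary outcomes in an open-label trial, which must be dated, justified and reported as such.

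No 2-week measure is proposed. The trial report can note that no symptom scale is listed at 2 weeks, so early symptom benefit was not assessed.

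### The maternal infection outcome counts perineal but not caesarean wound infection, so it loses events and means something different after caesarean and vaginal birth

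*Protocol article*

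**What the plan says.** Among the secondary outcomes, the Clinical outcomes section lists "Incidence of confirmed or suspected maternal infection within 6 weeks of birth" and defines it through a "new prescription of antibiotics for presumed perineal wound-related infection, endometritis or uterine infection, urinary tract infection or other systemic infection (clinical sepsis"). Four indications qualify: perineal wound, uterus, urinary tract, and systemic infection in the sense of clinical sepsis. No phrase marks these as examples, and no other section adds a surgical or abdominal wound. It is the only maternal infection outcome listed.

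Three other places bear on it:

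- **Eligibility criteria** admit "Women aged between 15 and 49 years and between 6 and 48 hours after birth" who meet the haemoglobin threshold. No exclusion refers to mode of birth.
- **Statistical methods and analysis** plans subgroup analyses by "mode of birth (caesarean vs vaginal birth) and by the occurrence of primary postpartum haemorrhage", as well as by region.
- **Background and rationale** states: "Postnatal anaemia increases the risk of infection and poor wound healing". It does not limit this to perineal wounds.

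**The concern.** The definition is written out site by site, so this is a stated rule and not a detail left to a fuller document. Followed literally, it codes a treated, localised caesarean wound infection as no infection. Three things are at stake:

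- **Events and precision.** Infections that led to antibiotic treatment are dropped from a secondary outcome that may have few events.
- **Coverage.** Infection and impaired wound healing are given as reasons to treat postpartum anaemia. The outcome that should reflect them leaves out the surgical wound of every caesarean participant. An effect of intravenous iron on that wound, in either direction, would show only in cases with sepsis or another listed infection.
- **Comparability between strata.** After vaginal birth the outcome includes infection of the birth wound. After caesarean it does not include infection of the incision.

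**Working it through.** **Textual check.** The document states no infection rate, power or sample size for this outcome, so there is no plan figure to reproduce. The sample size of 697 per group concerns anaemia at 6 weeks and has no bearing here. Take a woman prescribed new antibiotics for a localised infection of her caesarean incision and test her against each item:

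| Listed indication | Met? |
|---|---|
| Perineal wound | No: the wound is abdominal |
| Endometritis or uterine infection | No, unless also present |
| Urinary tract infection | No, unless also present |
| Other systemic infection (clinical sepsis) | No, unless it has become systemic |

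She has a treated postpartum infection and is coded as having none. A woman with an equally localised infection of a perineal wound is coded as a case.

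**Illustration of size.** None of these inputs comes from the document. All are assumptions, chosen to show a range:

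- caesarean share c = 20% to 50%
- antibiotic-treated caesarean wound infection among caesarean women w = 3% to 10%
- listed infections q = 8% in the control arm, whatever the mode of birth
- no overlap between wound infection and listed infections

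Share of infections missed among caesarean women = w / (q + w):

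- w = 3%: 0.03 / 0.11 = 27%
- w = 6%: 0.06 / 0.14 = 43%
- w = 10%: 0.10 / 0.18 = 56%

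Share missed overall = c·w / (q + c·w):

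- lowest: 0.20 × 0.03 = 0.006, and 0.006 / 0.086 = 7%
- highest: 0.50 × 0.10 = 0.05, and 0.05 / 0.13 = 38%

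Number of events lost among the 1400 women = 1400·c·w:

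- these ranges: 1400 × 0.20 × 0.03 = 8 to 1400 × 0.50 × 0.10 = 70
- a different but equally unsupported choice (c 20% to 40%, w 5% to 15%): 1400 × 0.20 × 0.05 = 14 to 1400 × 0.40 × 0.15 = 84

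The count therefore depends on the assumptions. Any overlap with sepsis, endometritis or urinary infection would lower it.

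**Effect on precision.** Take 700 × 0.9 = 630 analysed per arm (10% loss, as in the Sample size section), two-sided alpha 0.05, and an assumed relative risk of 0.7 for every type of infection. The normal approximation for two proportions gives:

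| Outcome | Control | Intravenous iron | Power |
|---|---|---|---|
| As published | 8.0% | 5.6% | 39% |
| With caesarean wounds, c = 20%, w = 3% | 8.6% | 6.0% | 42% |
| With caesarean wounds, c = 50%, w = 10% | 13.0% | 9.1% | 60% |

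The gain depends on iron acting on caesarean wound infection as it does on the other sites. If it had no effect there, counting those events would dilute the relative risk. Coverage and a consistent meaning would still argue for counting them.

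**The case against.** Several stronger readings are tempting, and the document does not support them.

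- **That the treatment comparison, overall or by mode of birth, is biased.** A reader might infer this from the unequal coverage. A subgroup analysis here compares the two randomised arms within each stratum, and both arms use the same definition. The contrast on listed infections stays valid in each stratum. The plan does not name infection as a subgroup outcome, nor does it plan to compare infection rates between caesarean and vaginal births. What stands is that, if infection is reported by mode of birth, the two strata do not measure the same thing as regards wounds.
- **That the list is complete for vaginal births.** It is not shown to be. Breast infection, for example, is unlisted for all women. The asymmetry concerns wound infection only.
- **That any effect on caesarean wounds is wholly hidden.** Cases with sepsis or another listed infection still count. Women are also asked about symptoms at each visit (Adverse drug event monitoring), but that record serves a separate outcome.
- **That caesarean wound infection is a main route of infection, or that a given number of cases is lost.** The document has no rates, so neither can be asserted from it.

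It can also be said that the case report form and full protocol are not shown, and that staff may in practice count caesarean wounds. If so, 20 sites are deciding against the stated rule in an open-label trial. Infection is not among the outcomes that the Blinding section assigns to blinded nurses. That favours explicit wording.

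Timing is the strongest practical objection. Recruitment was projected to end by June 2024. Six weeks (42 days) after 30 June is 11 August 2024, and the article appeared on 14 August. If the projection held, a new form option would capture almost nothing, and the correction depends on indications already recorded.

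**Conclusion.** The omission stands on the text. As defined, the secondary maternal infection outcome counts a localised caesarean wound infection treated with antibiotics as no infection, although caesarean women are enrolled and mode of birth is a planned subgroup. The consequences are lost events and precision, no coverage of surgical wound infection, and poor comparability of this outcome between strata as regards wounds. The randomised comparison is not biased by this alone, and the primary outcome and its sample size are untouched.

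The size cannot be derived from the document. The 27% to 56% missed among caesarean women, the 7% to 38% missed overall and the power figures all rest on the assumed rates shown, with no overlap between infection types. They show that the loss could matter, not how large it is. The conclusion also assumes that the published list is applied as written.

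**What to change.** Before outcome data are analysed by arm:

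1. Reword the wound item to *perineal or caesarean (abdominal) wound-related infection*. Keep the other items unchanged, including the restriction of systemic infection to clinical sepsis.
2. Check whether the case report form records antibiotic indications outside the present list. Where it does, classify existing records from the recorded indication, without knowledge of allocation. Where it does not, state how many prescriptions cannot be classified.
3. Report the outcome as published as a sensitivity analysis, and date and explain the change.
4. If infection is shown by mode of birth, give the site of infection so that the strata can be read side by side.

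The cost is a late change to one secondary definition and some recoding. No extra visits or participants are needed. Adding breast infection is optional: it would broaden the outcome and is not part of this error.
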